# Adolescent depression: Study protocol for a randomized, controlled, double-blind multicenter parallel group trial of Bright Light Therapy in a naturalistic inpatient setting (DeLight)

**DOI:** 10.1186/s13063-018-2949-0

**Published:** 2018-10-19

**Keywords:** Depression in youth, Treatment, Bright light therapy, Inpatients

## Abstract

**Background:**

Depressive disorders are among the most prominent health problems in youth. Even with the best available pharmacological and non-pharmacological treatments, remission rates are low. Without early treatment, depression in youth is associated with a high risk of symptom progression, chronicity, co-morbidity, and suicidal behavior. Thus, adolescent depression is a prime candidate for innovation in treatment. In depressive adults, meta-analytic evidence has proven that bright light therapy (BLT) is a potent low-threshold intervention, promising due to easy application, low side effects, and optimized compliance. In adolescents, studies with small samples show promising effects. This randomized controlled trial will examine the effectiveness of BLT in youth inpatients.

**Methods/design:**

In this randomized, controlled, double-blind multicenter parallel group trial, morning BLT is applied for four weeks in addition to treatment as usual (TAU) for depressed youth inpatients (daily morning exposure to bright light via light-emitting glasses, 10,000 lx, for 30 min) and will be compared to a control condition (placebo light treatment, red light, identical light glasses). The primary objective is to assess whether BLT reduces symptoms of depression in youth with greater effect compared to placebo light therapy. Secondary objectives are to examine the impact of BLT on responder status, application of antidepressant medication, and further depression-related symptoms (sleep, activity, quality of life, satisfaction with health, general psychopathology, alertness, and circadian function). *N* = 224 patients will be recruited in a naturalistic inpatient setting. A follow-up will be carried out after three and six months.

**Discussion:**

The study aims to discuss and evaluate BLT as an additive method supporting standardized clinical procedures dealing with severe to moderate depressive symptoms in youth.

**Trial registration:**

German Clinical Trials Register, DRKS00013188. Registered on November 30, 2017.

**Electronic supplementary material:**

The online version of this article (10.1186/s13063-018-2949-0) contains supplementary material, which is available to authorized users.

## Background

Depressive disorders are among the most prominent health problems in youth. In adolescents, prevalence rates of depression are in the range of 5–6% [1], with a lifetime prevalence rate of 20% by late adolescence [2]. Prevalence in girls is twice as high as in boys and higher symptom load is found in youth with a high number of psychosocial risks [3]. The five-year recurrence rate in adolescent depression is as high as 40% [4]. In addition, a depressive mood during the winter season is quite common among youth in central Europe, with at least 2% of adolescents and young adults meeting criteria for seasonal affective disorder (SAD), e.g. a clinically meaningful depression with a seasonal pattern [5]. Of all depressive youth, 10% receive inpatient treatment at least once. In Germany, inpatient treatment rates for adolescent depression have increased dramatically by > 200% from 2000 to 2007, compared to 38% for all mental disorders [6].

Adolescent depression may interrupt educational attainment and thus affect human capital accumulation and future earnings. Since teenage suicide, for which depression is a principal risk factor, is the second leading cause of death in German youth, preceded only by traffic accidents [7], it is important to acknowledge that the human costs associated with depression are in a real sense greater than the economic costs. Adolescent depression is a key risk factor for adult depression; it severely impairs work and school management, leisure activities, and social contacts; frequency and degree of disabilities in depressed youth are at least as pronounced as in adults [8]. In short, depression in adolescents is prevalent, of significant public health importance, and thus a prime candidate for innovation in treatment.

Despite a huge increase in treatment research in the past 20 years, remission rates of pharmacological treatments are low [9]. In the carefully designed gold standard studies TADS and TORDIA, remission rates for moderate to severe depression were < 40% after three and six months of combined medication and psychotherapy ([10, 11]). A recent meta-analysis yielded only small effect-sizes for selective serotonin reuptake inhibitor (SSRI) and serotonin and norepinephrine reuptake inhibitor (SNRI) treatment of depressive disorders in children and adolescents [12]. Treatment decisions are further complicated by safety concerns of antidepressant-related self-harm and suicide in youth [13]. Despite these problems, a doubling of prescriptions for antidepressants in German adolescents has been observed in recent years [14]. The current evidence- and consensus-based clinical practice guideline of the German Association for Child and Adolescent Psychiatry (DGKJP) for the treatment of adolescent depression concluded that due to “the glaring lack of clinical studies (…) there is a pressing need for intervention research” [15].

Within the last decade, especially in the field of adult psychiatry, evidence suggests promising effects of bright light therapy (BLT) with respect to the improvement of depression symptoms. We conducted a systematic overview regarding BLT for the treatment of both non-seasonal and seasonal depression by using a broad range of databases. The present search is an update of already published reviews by our group laying special emphasis on clinical trials of BLT in depressed adolescents ([16, 17]). In adults, recent meta-analytic evidence [18] has proven that BLT leads to a significant reduction of depressive symptoms in non-seasonal depression (SMD = − 0.62, *P* < 0.001). In particular, BLT appears to be efficacious when administered for 2–5 weeks (SMD = − 0.78, *P* < 0.001). The authors emphasize the obvious need to optimize the duration and intensity of exposure and the timing and duration of treatment sessions. In a Cochrane review on BLT in non-seasonal depression, studies with a higher methodological quality rating showed unequivocal superiority of BLT over control treatment (effect-size 0.90, 95% confidence interval [CI] 0.31–1.50 [19]). Of note, treatment duration in almost all included studies was brief (1–2 weeks). Existing evidence suggests that longer treatment (at least four weeks) yields larger effects.

Up until now, only very few studies investigated the effects of BLT on depression in youth (see [20] for a systematic review of studies until 2012 and [18] for meta-analysis including more recent trials). In one of our pilot studies [21], remission rates after two weeks of BLT (light box, 10,000 lx; *n* = 30) and a further three weeks of follow-up were 46.7% for BLT and 25.9% for dim light (100 lx; *n* = 27); however, these differences were not significant due to the small sample size. BLT significantly improved sleep difficulties in youth [21]. Sleep restoration occurred only during BLT and remained stable during follow-up, while dim light remained without any effect. BLT may, therefore, be especially suited for depressive adolescents, of whom 75% are affected by problems with the sleep-wake rhythm [22]. A combination of BLT and an additional night with sleep restriction did not result in greater symptom reduction than BLT alone in 60 adolescent depressive inpatients [23]. A secondary analysis with actigraphy and sleep diary data showed greater sleep-enhancing effects in the BLT group than the combined group after two weeks of intervention [24].

BLT is promising due to robust evidence in adults, easy application, low side effects, and heightened compliance [25]. Light glasses have been shown to lead to the same results as a 10,000 lx light box ([26, 27]). However, empirical evidence on BLT for youth is scarce and pilot studies suffer from small sample sizes, lack of randomization, shortness of treatment duration, and lack of control settings. Moreover, a combination of BLT and treatment as usual (TAU; including pharmacotherapy) might be promising, because more naturalistic studies taking into account antidepressants do not exist. The proposed trial shall extend the pilot findings; treatment duration will be prolonged to four weeks to yield larger effects and follow-up will be extended to six months. Results of the proposed trial should allow conclusions as to the acceptability, the effects, and the costs of BLT in youth, thus providing a basis for decisions as to the broader implementation. We assume that BLT should lead to more robust symptom remission, potentially facilitating dose reduction or even replacement of antidepressants and a subsequent lower risk of adverse events (AEs). BLT may lead to a faster onset of effect [28], leading to shortened hospitalization, and can prevent transition to more severe forms of depression.

The projected trial will:examine whether BLT (daily morning exposure, 10,000 lx, for 30 min) in addition to multimodal TAU reduces symptoms of depression in youth inpatients with greater effect compared to placebo light therapy plus TAU (red light);assess the impact of BLT on responder status, application and dosage of antidepressant medication, and further depression-related symptoms (sleep, activity, quality of life, satisfaction with health, general psychopathology, alertness, circadian function), and length of stay in hospital;assess the prevalence and severity of BLT side effects which have been vastly neglected in previous studies.

## Methods/Design

### Study rationale

This trial is a randomized, controlled, double-blind multicenter parallel group study. The trial protocol has been approved by the medical ethics committee of the Ruhr-University Bochum, Germany (registration number 17–6140-BR) and is registered with the German Clinical Trials Register (DRKS00013188). The trial will be conducted according to the principles of ICH-GCP and appropriate legal regulations. The Professional Code for Physicians in Germany and Declaration of Helsinki in its actual version will be adhered to. For recommended items to address in a clinical trial protocol according to the SPIRIT 2013 Checklist, see "Additional file 1". 

### Study setting and recruitment

Four Departments of Child & Adolescent Psychiatry of the Universities/Medical Schools of Bochum, Ulm, Hamburg, and Brandenburg/Neuruppin participate in the study and will recruit inpatients. The study sample should reflect everyday clinical practice to be as representative as possible for inpatient youth (aged 12–18 years) with moderate to severe depression [29]. Diagnoses will be ascertained by structured clinical interviews. To maximize generalizability (i.e. testing for effectiveness), exclusion criteria are limited to situations that would prevent full participation in the study or that might require additional treatment incompatible with study treatments. Inclusion and exclusion criteria are listed in Table 1. Antidepressant medication is allowed and controlled for in the analyses performed (naturalistic approach).

**Table 1 Tab1:** Inclusion and exclusion criteria

Inclusion criteria	Moderate to severe depression (BDI-II)
	Inpatients aged 12–18 years
	Written informed consent of the inpatient and the caretaker
Exclusion criteria	Acute suicidality, bipolar 1 disorder, or schizophrenia
	Pregnancy or lactation
	Treatment with beta-blocker or with high-potency neuroleptics
	Diseases of the retina
	IQ < 70
	Non-German-speaking child or caretaker

*BDI-II* Beck Depression Inventory II

### Informed consent process

First, patients and parents will be informed in written and oral forms regarding the study, the procedures, and the potential risks or discomforts and potential benefits. An informed consent document with details about the study including its purpose, duration, procedures, and key contacts, as well as risks and potential benefits, will be handed out to patients and parents. The patients and parents will then decide whether to give written consent. Patients or parents unwilling or unable to consent will not be included in the study. At any time, participants or parents may withdraw their consent for any reason without any negative consequences regarding their treatment.

### Randomization and blinding procedures

Potential bias is minimized by randomized treatment allocation and by blinded outcome assessment. Since patients will be blinded towards their treatment, patient-reported outcomes including the primary outcome will be blinded. Independent raters unaware of the patient’s treatment will perform further assessments (CDRS-R). Randomization is performed using the electronic case report form and will be stratified by prior pharmacological antidepressant therapy (yes/no), trial site, and sex. The randomization ratio will be 1:1 based on blocks of variable length.

Patients and clinical raters will both be blinded regarding treatment allocation. While the primary outcome (BDI-II) will be rated by the blinded patients themselves, the clinical evaluation (CGI-I, CDRS-R) will be performed by the blinded clinician. Blinding will be assured by separating diagnostic procedures from general patient and data handling. There will be one research assistant organizing recruitment and all patient-relevant data handling as well as a second person solely performing the diagnostic assessments. This procedure has proven to be feasible in our pilot study [21].

### Experimental / control condition

Finding an appropriate control condition for light therapy to minimize placebo effects is difficult, since these effects are expected to be quite high in depression. In the projected study, the active light treatment will consist of daily morning exposure to white fluorescent light (light glasses Luminette®; 10,000 lx) for 30 min for 28 days (weekends excluded), while the placebo treatment will be provided by identical glasses with a red light without known effects on depression. This design has been shown to be feasible in adolescents [21]. Since light therapy is most effective if applied at an optimal time in the circadian phase of the patient, light interventions will be carried out 7.5–9.5 h after the individual evening melatonin onset (DLMO) estimated by the Morningness–Eveningness Questionnaire (MEQ) [30, 31].

### Interventions

Following feedback from the participants in our pilot studies, light boxes are replaced by light glasses that allow patients to carry on with everyday tasks and fit into their daily routine while giving the same results as a 10,000 lx light box ([26, 27]). To ensure an appropriate and constant number of lux administered in each condition, intensities are quantified using a Lux meter (PCE-172). If a patient is not able to receive the intervention on a given day (e.g. due to illness), he is committed to prolong the intervention phase for one day. In case of several missing interventions (max. 20% of the sessions), the patient will be excluded from the study. In order to control for placebo effects, the therapy expectancy and credibility questionnaire will be administered in a modified version before treatment.

Study interventions will be added to a naturalistic multimodal inpatient TAU. TAU will be documented in detail: due to the requirements of the recently introduced new reimbursement system for psychiatric hospitals in Germany, the participating centers are already documenting continuously type, frequency, and duration of patient-directed interventions electronically for all relevant professions (psychiatrists, psychotherapists, nurses, occupational therapists, etc.). These data can be aggregated for participants of the projected study to determine the distribution among groups.

In some cases, psychopharmacological antidepressant treatment may be warranted and will be provided according to the attending physician’s clinical judgment (non-interventional). Afternoon outdoor activities are part of a comprehensive youth inpatient care but are unlikely to interfere with the antidepressant response to BLT, since treatment response is maximized if BLT is initiated no later than 8.5 h after a patient’s estimated melatonin onset, e.g. only in the early morning. Light exposure at midday or in the afternoon does not result in an antidepressant effect [32].

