### Intervention scheme / trial flow

Inpatients from all trial sites that meet the inclusion criteria and give informed consent are consecutively included into the trial within one week after admission. After inclusion, inpatients will be interviewed by the blinded research psychologist. Initial self-report measurements and objective data in relation to depression and associated co-morbidity as well as medication are assessed by a trained diagnostician. In addition, treatment expectancy and responsibility to seasonal effects will be assessed. After the pre-treatment assessment (T1), patients are randomized to either a placebo control condition (PCC) or BLT. Both groups also receive TAU. Trial interventions will be delivered each morning (except weekends) over a period of four weeks about 7.5 h after the DLMO assessed with the MEQ.

During the intervention trial, an interim assessment with the BDI-II after two weeks will take place in order to control patient-perceived changes in depression more closely. There is no full assessment in order to reduce stress for the patients. Four weeks after completion of the treatment, individuals will again be interviewed by the blinded research psychologist and score the self-rating questionnaires as well as perform the neuropsychological assessment and deliver saliva melatonin and cortisol (post-treatment assessment; T2). Three and six months after T2, follow-up assessments will be performed via telephone and questionnaires to control for stability (T3 and T4). There is no full reassessment for neurobiological and neuropsychological data in order to facilitate the response to fulfil the follow-up assessment and to meet patients’ needs best. Moreover, AEs will be assessed in both treatment groups on a weekly basis. For an overview of the trial flow, see Fig. 1. For details on procedures per time point, see Figs. 2 and 3.

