### Data analysis

#### Proposed sample size/power calculations

In our pilot study [20], a similar trial design was used, investigating the effects of BLT versus placebo light therapy after a treatment period of 14 days and a follow-up period of three weeks. Remission rates at the end of follow-up (week 5) were 46.7% for BLT and 25.9% for dim light. These remission rates were transformed (2*arcsin; √remission rate). The difference between the transformed remission rates resulted in Cohens h of 0.437 and was used for the calculation of the study sample. A significant difference between the two groups is defined as 3 points on the BDI-II by the NICE guidelines. A standard deviation of 10 points in the BDI-II is assumed. Thus, the proposed study aims to show a group difference of 4.37 points on the BDI-II. Calculations based on this difference yield a sample size of 224 patients (112 for each group) when using an independent t-test at a significance level of 5% and a power of 90%. Sample size was calculated using PROC POWER in SAS® Version 9.4. Drop-outs will be analyzed using multiple imputation methods.

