#### Statistical analyses

The primary analysis population is the intention-to-treat (ITT) population comprising all randomized patients. Group difference in change of BDI-II rating under trial treatment will be analyzed by an analysis of covariance (ANCOVA) comprising the covariates baseline BDI-II rating, treatment group, prior pharmacological antidepressant therapy (yes/no), and sex. Missing values will be replaced by multiple imputation. The two-sided level of significance will be α = 5%. Supportive analyses are planned for the Per Protocol Population and the Completer Population. The Per Protocol Population comprises all patients from the ITT population without major protocol violations: lack of compliance with regard to therapy sessions; not meeting all inclusion criteria; meeting at least one exclusion criterion; intake of unallowed concomitant medication during the study; end of treatment visit out of schedule. In an additional sensitivity analysis, missing values will be analyzed based on the last available BDI-II rating (Last Observation Carried Forward [LOCF]). In case the LOCF approach turns out to be not conservative, an additional Baseline Observation Carried Forward (BOCF) analysis will be performed.

Further subgroup analyses are planned to detect possible differences between predictive factors (e.g. trial site, concomitant psychotropic medication for co-morbid disorders, baseline CAR and DLMO, type of depression [seasonal/non-seasonal], season, expectancy questionnaire). No interim analyses are planned. Secondary endpoints will be analyzed descriptively applying appropriate methods depending on the scale of the respective parameter. Interpretation of statistical tests must be exploratory except for the primary outcome.

AEs will be coded according to MedDRA terminology. Detailed information collected for each AE will include: a description of the event; duration; whether the AE was serious; intensity; relationship to trial treatment; action taken; and clinical outcome. Summary tables will present the number of participants observed with AEs by MedDRA System Organ Class and Preferred Term and corresponding percentages. Additional subcategories will be based on event intensity and relationship to trial treatment. A subject listing of all AEs will be prepared.

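### Excluding patients from the study for missed sessions is an adherence-based exclusion after randomisation; it must be reconciled with the all-randomised primary analysis, and outcome assessment should continue for these patients

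*Protocol article*

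**What the plan says.** All references are to the protocol article.

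- **Interventions.** A patient who cannot have a session on a given day makes it up: "he is committed to prolong the intervention phase for one day". For more than isolated misses the rule is: "In case of several missing interventions (max. 20% of the sessions), the patient will be excluded from the study".
- **Intervention scheme / trial flow.** "After the pre-treatment assessment (T1), patients are randomized to either a placebo control condition (PCC) or BLT". Sessions follow: "Trial interventions will be delivered each morning (except weekends) over a period of four weeks". A BDI-II is also taken after two weeks.
- **Statistical analyses.** "The primary analysis population is the intention-to-treat (ITT) population comprising all randomized patients". "Missing values will be replaced by multiple imputation". The Per Protocol population is formed from the ITT population by removing major violators, and the first violation listed is "lack of compliance with regard to therapy sessions". LOCF is a sensitivity analysis, with BOCF added if LOCF proves not to be conservative.

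The article does not say whether a patient excluded for missed sessions still has the BDI-II and the other assessments at T2, T3 and T4.

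**The concern.** The same behaviour has two different consequences. In one section a patient who misses too many sessions leaves the study. In the other, that patient stays in the primary analysis population and leaves only the Per Protocol set. The second treatment already deals with non-compliance, so exclusion from the study adds nothing to the analysis except missing outcomes.

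A site that follows the Interventions section literally has no reason to bring these patients back for T2. Their primary endpoint is then never observed, and no later analysis plan can recover it. Multiple imputation under the usual missing-at-random assumption would predict their values from patients who kept attending, given whatever else is in the model. That assumption is doubtful when the reason for being missing is poor attendance. LOCF and BOCF substitute other values for the missing one; they do not restore an observed outcome.

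**Working it through.** **1. Timing.** T1, then randomisation, then sessions. An exclusion triggered by missed sessions can therefore only occur after randomisation.

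**2. The plan's own sample size.** Inputs from the section on sample size: "the proposed study aims to show a group difference of 4.37 points on the BDI-II", SD 10, 5% level, 90% power, independent t-test; two-sided according to Statistical analyses.

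- Noncentrality with n per arm = 4.37 / (10 × √(2/n)). For n = 112 this is 4.37 / 1.336 = 3.27.
- The noncentral t distribution with 222 degrees of freedom gives power 0.9025. The stated 112 per arm, 224 in total, is reproduced.
- That number contains no allowance for lost outcomes.

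**3. Equal loss in both arms.** Assume the same share is excluded in each arm, with the same outcome deficit, and that only observed T2 values count. The bias is zero (step 4) and power falls:

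| Share lost | n per arm | Power |
|---|---|---|
| 0% | 112 | 0.90 |
| 5% | 106 | 0.886 |
| 10% | 101 | 0.871 |
| 15% | 95 | 0.850 |
| 20% | 90 | 0.830 |
| 25% | 84 | 0.804 |

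**4. Unequal loss.** Let a share e of an arm be excluded, let excluded patients improve D points less than retained patients of the same arm, and let imputation treat them like retained patients.

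- True arm mean = (1 − e) × m + e × (m − D) = m − eD, where m is the retained mean.
- The analysis uses m, so each arm is too favourable by eD, and the bias in the group difference is (e_BLT − e_PCC) × D.
- With 20% against 10%: D = 5 gives 0.10 × 5 = 0.50 points, and D = 8 gives 0.10 × 8 = 0.80 points. These are 11% and 18% of 4.37.
- Under no true effect, with 89.6 and 100.8 patients observed, the nominal 5% error becomes about 6.4% and 8.5%.
- If the larger share is lost from the placebo arm, the sign reverses.

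**5. Upper case.** Assume 20% excluded, no effect at all in them, 4.37 points in everyone else, and imputation that gives the excluded the full effect.

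- All-randomised effect = 0.80 × 4.37 = 3.50.
- Reported effect = 4.37, and 4.37 / 3.50 = 1.25.

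None of the exclusion shares or deficits in steps 3 to 5 is in the article; all are assumptions.

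**The case against.** The strongest reply is that the analysis section already gets this right. It keeps every randomised patient in the primary population, imputes what is missing, and removes non-compliers only from the Per Protocol set. That stands. A reader might infer that non-compliers are dropped from the ITT analysis, and the article does not say so. It also does not expressly say that assessments stop; that is the plain reading of exclusion from the study, but an inference. Exclusion could have been meant as the end of light sessions only.

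Several stronger readings are tempting and do not hold:

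- **The primary estimate simply becomes a complier estimate, overstated by 25%.** This needs zero effect in every excluded patient and full-effect imputation. A patient only just over the limit has had almost 80% of the sessions, and the make-up rule should make reaching the limit less common. The figure is an upper case.
- **Early improvers are lost and the effect is diluted.** Suppose patients leave because of large improvement by week 2, about 16% of the light arm and 11% of the placebo arm. The raw difference among retained patients then falls from 4.37 to about 3.7. The planned analysis is not that raw comparison, however. Imputing within arm from the week-2 BDI-II, which the trial collects, gives 4.36. The article does not fix the imputation model, so this bias cannot be claimed.
- **Early discharge triggers the rule and length of stay is lost.** The article does not count discharge as missed sessions, and length of stay is an administrative item that hospitals hold anyway.
- **The trigger is four of 20 sessions.** Four weeks of weekdays give 20 sessions, and 20% of that is 4. The maximum may mean that four misses are tolerated. If the 28 days stated under Experimental / control condition were read as 28 sessions, 20% would be 5.6.

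What remains is the mismatch between the two sections, and the likely loss of primary-endpoint data under the rule as written.

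**Conclusion.** The concern holds in this form: a stated rule, acting after randomisation and depending on adherence, does not fit the all-randomised primary analysis. On its plain reading it loses T2 to T4 outcomes in the patients for whom imputation is least secure. This is more than detail left to an analysis plan, because values never collected cannot be supplied later.

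Size and direction are not known. If exclusion rates and outcome deficits are equal in both arms, the cost is power only. If they differ, the illustrations in the working give a bias of about half a point to just under one BDI-II point, in either direction according to which arm loses more. The case of 4.37 reported against 3.50 marks an upper end and is not an expected result. If the sponsor meant only that light sessions end while assessments continue, the wording is still wrong but no outcome data are lost.

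**What to change.** In Interventions, replace the clause on exclusion from the study with wording to this effect:

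> A patient who meets the missed-session criterion is recorded as having a major protocol violation and is removed from the Per Protocol population only. The BDI-II and the other planned assessments are carried out at T2, T3 and T4 for every randomised patient, unless consent is withdrawn.

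The same sentence should define the criterion for the Per Protocol set: the planned number of sessions, whether it applies at or above 20%, and whether made-up days count as missed. Whether and when light sessions stop is a separate matter for the sponsor to decide and to state separately.

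The cost is a change of wording and a few more questionnaires and assessments from patients already enrolled.
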